# Advancing sustainable implementation of an evidence-based mental health intervention in Sierra Leone’s schools: protocol for a hybrid type 3 implementation-effectiveness trial

**DOI:** 10.1186/s12889-024-17928-w

**Published:** 2024-02-03

**Keywords:** Implementation science, Mental health, Youth, Low-resource settings

## Abstract

**Background:**

Mental health disorders among youth contribute substantially to the global burden of disease, which is exacerbated in low- and middle-income countries (LMICs) due to large mental health treatment gaps. In Sierra Leone, a West African country with a long history of complex adversity, the mental health treatment gap is estimated at 98%. Implementing innovative mental health interventions that can be sustained at scale is a priority. The Youth Readiness Intervention (YRI) is an evidence-based mental health intervention for youth that can be delivered feasibly by lay health workers/nonspecialists. Using mobile-based technologies to assist implementation could improve the reach and sustainability of the YRI in Sierra Leone. This study aims to train teachers to deliver the YRI in Sierra Leone’s secondary schools and test the feasibility, acceptability, cost, and fidelity to the YRI of a mobile-based supervision model compared with standard, in-person supervision.

**Methods:**

We will conduct a hybrid type 3 implementation-effectiveness cluster randomized trial to assess the feasibility, acceptability, costs and fidelity to the YRI implemented by teachers receiving mobile-based supervision vs. standard supervision. Enrolled schools (*N* = 50) will be randomized to YRI + mobile supervision (*N* = 20), YRI + standard supervision (*N* = 20) or waitlist control (*N* = 10). We will recruit and enroll four teachers per intervention-condition school (*N* = 160) and 1200 youth. We will collect data on implementation outcomes among teachers, principals and youth via a mixed methods approach at baseline and post-intervention. We will also collect quantitative data on youth mental health and functioning as secondary outcomes at baseline and post-intervention, as well as cost-effectiveness data at 12-month follow-up.

**Discussion:**

Study findings have the potential to expand the reach of mental health services among youth in low-resource settings via a teacher workforce. The use of mobile tools, if successful, could support further scale out and sustainment of the YRI to other regions of Sierra Leone and West Africa more broadly, which could help address the mental health treatment gap.

**Trial registration:**

Clinical Trial Network: NCT05737667.

**Supplementary Information:**

The online version contains supplementary material available at 10.1186/s12889-024-17928-w.

## Background

The global burden of disease attributed to mental health disorders among youth and adults is compounded in low-and middle-income countries (LMICs) and other low resource settings due to the wide mental health treatment gap. This is especially problematic in LMICs with a history of violence and loss [1–3]. In Sierra Leone, a country in West Africa that has experienced a long history of compounded adversity (i.e., civil war, the Ebola epidemic), the mental health treatment gap is estimated at 98%, with 49.4 disability adjusted life years per thousand population lost among youth aged 15–29 due to mental health and substance use disorders [4]. Significant limitations in the nation’s health infrastructure have made it difficult to effectively address the population’s unmet mental health needs [4–6]. Given both the limited healthcare infrastructure in Sierra Leone and the high level of mental health needs among youth, identifying alternative delivery settings in which evidence-based mental health interventions can be feasibly delivered by lay workers—both with quality and at sustainable scale—is a priority.

The education sector is a strong option to address the mental health needs of the burgeoning youth population in Sierra Leone by leveraging the teacher workforce and providing strong supervision and training for delivery of evidence-based mental health interventions in schools [7–9]. Prior research in Sub-Saharan Africa supports the feasibility and efficacy of task-shifting strategies that involve teachers as delivery agents to address human resource barriers to mental health service delivery [10–13]. Exploring schools as an alternative delivery setting for evidence-based mental health interventions delivered by a teacher workforce could improve the reach of mental health services for underserved youth and the ability of youth to actualize educational and employment opportunities [14–16]. This also aligns with the priorities of the Government of Sierra Leone to invest in human capital through empowering their youth population (61% of Sierra Leoneans are under age 25) and including student mental health and wellbeing as a strategic priority in their Education Sector plan [8].

In prior research responding to the lack of mental health services in Sierra Leone, a transdiagnostic, common elements-based intervention, the *Youth Readiness Intervention* (YRI), was developed using community-based research methods to promote the mental health of Sierra Leonean youth who had been affected by violence and adversity [17]. The YRI integrates core components of cognitive behavioral therapy, interpersonal therapy, and mindfulness-based techniques and focuses on improving problems with emotion regulation, interpersonal deficits, and problem-solving skills (See Fig. 1) [17, 18]. The YRI has demonstrated effectiveness in improving mental health and daily functioning among vulnerable youth (aged 15–24) enrolled in an alternative education program and was feasibly delivered with quality by lay health workers [18]. Youth who received the YRI exhibited better classroom behavior and were six times more likely than control youth to persist in school. Data from both a pilot study and larger hybrid-implementation-effectiveness trial on the YRI delivered to youth enrolled in an employment promotion program also support the YRI’s mental health benefits [19–21].

**Fig. 1 Fig1:**
[figure not shown]
YRI Conceptual Model

The YRI is a promising and scalable approach to targeting underlying risk factors (e.g., poor emotion regulation) related to the onset of mental health problems among youth. Its demonstrated effectiveness in prior research and its simple, transdiagnostic elements make it highly suitable for delivery in resource-constrained community settings (i.e., schools in Sierra Leone) by a range of lay workers with a basic level of education. However, as with other evidence-based mental health interventions in LMICs, the YRI requires innovative implementation strategies for effective scale out and sustainment. Mobile-based strategies to build service delivery capacity and monitor intervention fidelity, particularly those that leverage widely available free commercial applications, have the potential to reduce long-term fiscal and human labor costs associated with traditional modes of supervision in person or via phone; thus, enabling greater scalability in settings with limited behavioral health professionals [22–24]. Applying mobile tools to build teachers’ ability to deliver the YRI’s evidence-based components with fidelity and completence could help decrease the added burdens associated with traditional modes of supervision (e.g., transportation, time) and improve the ultimate sustainability of the YRI within schools in Sierra Leone.

### Study aims

This study will implement the evidence-based YRI as an extracurricular resilience-building activity for youth in Sierra Leone’s secondary schools and train teachers to deliver the intervention. Teachers will receive either mobile phone-based supervision or standard in-person supervision to deliver the YRI. Mobile-based supervision will integrate WhatsApp with an mHealth app designed to support fidelity monitoring and feedback during supervision. Study aims are to: (a) examine the feasibility, acceptability, cost, and fidelity to the YRI delivered by teachers receiving mobile-based supervision compared with those receiving standard supervision; (b) compare the effectiveness of the YRI delivered in schools by teachers who receive either mobile-based supervision or standard supervision; (c) investigate potential mechanisms of YRI adoption and sustainment within schools, including readiness to change and organizational climate; (d) conduct a cost-effectiveness analysis to evaluate the relative costs vs. benefits of the YRI delivered in secondary schools with mobile-based supervision and standard supervision from a broad societal perspective, including educational outcomes.

We hypothesize that: (a) mobile-based supervision will be more feasible, acceptable, and cost-effective than standard supervision, and YRI fidelity scores for mobile supervision will be comparable to standard supervision; (b) youth mental health, emotion regulation, and daily functioning outcomes in mobile supervision will not differ from those in standard supervision over time; (c) readiness to change, organizational climate, and teacher buy-in will moderate YRI adoption and sustainment; (d) the YRI incremental cost-effectiveness ratio in both conditions will surpass the standard willingness to pay threshold [16].

### Study design

We will conduct a hybrid type 3 implementation-effectiveness cluster-randomized trial design [25] to investigate mobile-based supervision of YRI delivery by teachers in Sierra Leone’s secondary schools as a new implementation strategy, with clinical outcomes of the YRI on youth mental and behavioral health as secondary outcomes. We will use a mixed methods approach to investigate study aims. The Exploration, Preparation, Implementation, Sustainment (EPIS) framework [26], a broad, context sensitive implementation science process model, will guide study implementation. Randomization to study condition will occur at the level of the school. Schools (*n* = 50) will be randomized to YRI with mobile-based supervision (*n* = 20 schools/*n* = 480 youth), YRI with standard (in-person) supervision (*n* = 20 schools/*n* = 480 youth) or control (*n* = 10 schools/*n* = 240 youth). Control schools are necessary primarily for the cost-effectiveness analysis because they will provide reference level estimates of QALYs gained by intervention schools. We selected an unequal randomization design to reduce the number of youths who are exposed to the waitlist control [27]. We will offer YRI training to interested teachers in control schools following 12-month follow-up data collection. To optimize comparability between schools, we will match schools into quintets using an algorithm prior to randomly assigning two members of each quintet to each supervision model and the fifth to the control. All research assistants and data analysts will be blinded to participant assignment and will assign schools to study condition based on the allocation sequence.

Regarding standard reporting, this study will adhere to the Standard Protocol Items: Recommendations for Intervention Trials (SPIRIT) guidelines (See Fig. 2) and the Consolidated Standards of Reporting Trials (CONSORT). This trial is registered with the Clinical Trials Registry maintained by the National Library of Medicine at the National Institute of Health (Trial ID: NCT05737667; registered on 02/02/23). This study is approved by the Brown University Institutional Review Board (Protocol #2,022,003,442) and the Sierra Leone Ethics and Scientific Review Committee. Any subsequent modifications will be reviewed by both of these review committees for approval and then submitted to the Clinical Trials Registry as an amendment. The study protocol was also eviewed as part of the funding application.

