We will recruit 480 youth from the 40 secondary schools randomized to receive the YRI delivered with mobile supervision and 480 youth from schools that will receive YRI delivered with standard supervision. We will enroll 240 youth from 10 control schools. We will aim to recruit 24 youth per school, with two YRI groups per intervention school. We aim to recruit an equal number of male and female participants, as the YRI is delivered in separate groups for males and females. The target sample size of 1200 youth is powered to account for 10–20% attrition per our prior experience in Sierra Leone. Youth inclusion criteria are: (a) currently enrolled in a secondary school in the Western region; (b) male or female aged 14–24; (c) able and willing to attend an extracurricular school activity. Parental consent and youth assent will be obtained for all youth under age 18.

Our target age for enrollment of youth (aged 14–24) is based on prior research on the YRI demonstrating that the intervention is effective with male and female populations within this age range [19, 20]. Including students 18–24 reduces potential bias towards those youth who take longer to complete secondary school, delayed entry into school, or dropped out of school and later returned. Excluding students older than age 24 ensures we are targeting the developmental window of youth as defined by the United Nations and the World Health Organization.

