### Data analysis

#### Quantitative analysis

We will compare fidelity trajectories of teachers receiving mobile supervision to those of teachers receiving standard supervision and investigate the null hypothesis that mobile supervision will not differ from standard supervision. We will conduct exploratory analyses to uncover typical trajectories for each supervision method (mobile-based or standard) and undertake comparisons using growth curve modeling by means of multilevel models [44]. We will use HLM software (v.8.2), which estimates multiple imputations based on the dependencies of multilevel data. Missing time points are addressed by the multilevel approach to growth modeling, and data from all enrolled participants can be analyzed in accordance with our intention to treat design. The null hypothesis is that the outcomes for the mobile supervision YRI groups will not differ from those in standard supervision YRI groups. With this approach, we can compare both YRI models (as identified by dummy variables) to the untreated control group or assess the null hypothesis of no difference between the fidelity in the two models (mobile-based vs. standard supervision).

We will also investigate the null hypothesis that mobile supervision will not differ from standard supervision at post-intervention in youth outcomes. To investigate YRI effects on mental health among youth at post-intervention, we will use multilevel models to accommodate the clustering of students within YRI groups. For analysis of student outcomes, student characteristics will be modeled in a level-one equation. The group characteristics will be modeled in the level-two equation. School characteristics will be incorporated into a third level.

However, we do not expect a significant school-level intraclass correlation (ICC) for targeted YRI outcomes. In the event we do not find a significant ICC, sector and rural/urban will be represented in the group-level equation, and a two-level model will be estimated.

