#### Statistical power analysis for student outcomes

Power will be sufficient to assess our secondary aim and examine the hypothesis that the YRI delivered by teachers participating in mobile supervision will be noninferior in terms of youth mental health outcomes compared to the YRI delivered by teachers receiving standard supervision. At a power of 0.8 and an alpha of *p* <.05 (one-tailed to assess noninferiority), using an ICC of 0.03 (based on prior ICCs for mental health outcomes of 0.01-0.04) [18] for the group for comparisons at a single time point (post-intervention or 12-month follow-up) for student outcomes, the minimal detectable standardized effect size for a standardized difference (d) between the two of 0.21; in other words, at a negative difference of 0.21 or smaller, mobile supervision will be considered noninferior to standard. To test individual null hypotheses that either YRI implementation model (20 schools per YRI supervision mode) is superior (one-tailed) to the 10 untreated control schools with regard to mental health or educational outcomes, we have 0.8 power to detect a standardized effect of 0.26. In a comparison of all 40 YRI schools as compared to the 10 control schools, the minimum detectable effect would be 0.21.

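### Schools are randomised within matched quintets, but no stated model has a quintet term, and the youth model does not name the baseline score

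*Protocol article*

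**What the plan says.** **Randomisation (Study design).** The article states that "we will match schools into quintets using an algorithm prior to randomly assigning two members of each quintet to each supervision model"; the remaining school in each quintet is the control. With 50 schools this makes ten quintets, each split 2:2:1.

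**Youth model (Quantitative analysis).** The model is for outcomes at post-intervention and is laid out level by level. At the bottom, "student characteristics will be modeled in a level-one equation"; group characteristics come next; then "School characteristics will be incorporated into a third level". The authors do not expect a significant school-level ICC. If none is found, they will fit a two-level model with sector and rural/urban moved to the group equation. The quintet appears in neither version, nor in the description of the fidelity growth model.

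**Baseline score.** Data collection has all youth assessed on mental health and functioning at baseline and post-intervention. The model description does not name the baseline score. The power section works "for comparisons at a single time point (post-intervention or 12-month follow-up) for student outcomes".

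**The concern.** When randomisation is restricted by matching, the arm difference varies only with the variance left within quintets. A model without the quintet keeps the between-quintet variance in its error term, so its standard error does not describe the randomisation that was carried out.

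The direction of the error matters here. The Study aims hypothesise that youth outcomes under the two supervision modes will not differ, and Quantitative analysis tests a null of no difference. A standard error that is too large makes that hoped-for result easier to reach. In the one-tailed noninferiority test of the power section it acts the other way and costs power.

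The fallback adds a second risk. It can remove the unit that was randomised, and the standard error may then be too small.

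The baseline score is a matter of efficiency. It is already being collected, and with only ten control schools chance imbalance at baseline would otherwise pass into the comparison of YRI with control.

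**Working it through.** **Inputs from the article**
- Schools and youth: "Schools (*n* = 50) will be randomized to YRI with mobile-based supervision (*n* = 20 schools/*n* = 480 youth", the same for standard supervision, and 10 schools with 240 youth for control.
- Cluster size: "We will aim to recruit 24 youth per school, with two YRI groups per intervention school", so m = 24 per school and about 12 per group.
- Error rates: "At a power of 0.8 and an alpha of *p* <.05 (one-tailed to assess noninferiority".
- Clustering: "using an ICC of 0.03 (based on prior ICCs for mental health outcomes of 0.01-0.04".

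**Inputs not in the article, taken as ranges**
- q, the share of between-school variance explained by quintet: 0 to 0.75.
- r, the baseline-to-post correlation: 0.3 to 0.7, taken to be the same at student and school level.
- The ICC of 0.03 is placed at school level. The article states it for the group, but this placement is the one that reproduces its one-tailed figures.

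**1. Reproducing the plan's figures**

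SE = sqrt(2 × (0.03 + 0.97/24) / 20) = sqrt(2 × 0.07042 / 20) = 0.0839.

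Detectable difference = (1.645 + 0.842) × 0.0839 = 0.209, against the stated 0.21.

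One YRI arm against control: 2.487 × sqrt(0.07042 × (1/20 + 1/10)) = 0.256, against the stated 0.26.

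Neither figure uses a quintet or baseline term, so the planned precision takes no credit for either.

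**2. Quintet ignored, school level kept**

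True SE = sqrt(2 × (0.03(1 − q) + 0.97/24) / 20), while the model reports about 0.0839. One-sided type I error is 1 − Φ(1.645 × ratio).

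| q | True SE | Reported / true | One-sided type I error | Detectable difference with quintet modelled |
|---|---|---|---|---|
| 0 | 0.0839 | 1.00 | 5.0% | 0.209 |
| 0.25 | 0.0793 | 1.06 | 4.1% | 0.197 |
| 0.5 | 0.0744 | 1.13 | 3.2% | 0.185 |
| 0.75 | 0.0692 | 1.21 | 2.3% | 0.172 |

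A simulation of school means with t tests agrees. Power at a difference of 0.21 is 81%, 82% and 84% with the quintet ignored, and 83%, 87% and 91% with it modelled, for q = 0.25, 0.5 and 0.75. At q = 0, adding the quintet costs less than half a percentage point of power.

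**3. School level dropped by the fallback while the 0.03 sits at school level**

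The 40 groups per arm are treated as independent: model SE = sqrt(2 × (0.03 + 0.97/12) / 40) = 0.0744.
- q = 0: true SE 0.0839, ratio 0.89. The SE is understated by about 11%, and one-sided type I error is 1 − Φ(1.645 × 0.887) = 7.2%.
- q = 0.5: true SE 0.0744. The two errors cancel.

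**4. Baseline score left out**

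Detectable difference with baseline = 0.209 × sqrt(1 − r²): 0.199 (r = 0.3), 0.181 (r = 0.5), 0.149 (r = 0.7). Without baseline the SE is larger by 1/sqrt(1 − r²), that is by 5% to 40%, but it is still a correct SE for the unadjusted estimator.

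**The case against.** **Silence in a condensed article.** Covariate lists are commonly left to the analysis plan, and the unspecified student characteristics at level one could include the baseline score. This stands for baseline, which is unnamed rather than excluded. It stands less well for the quintet: the article fixes the levels of the model and the fallback covariates, and both leave out the restriction that its own design section imposes.

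**No general direction.** A reader might infer that the standard errors are simply too large. The documents do not support that. It requires matching that predicts outcome and a retained school level, and the authors' expected route is the two-level model, where the error can reverse. If the true school-level ICC is near zero, the quintet has almost nothing to explain. If sector and rural/urban drove the matching algorithm, which is not described, the fallback covariates would recover part of the variance.

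**Planned power is unaffected.** The stated 0.21 and 0.26 hold without either term, and an inflated SE is conservative for noninferiority. Both points stand. What is lost for that test is extra precision.

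**Loss to follow-up.** A reader might also infer that youth missing at post-intervention fall out of the analysis. The text does not say so. Quantitative analysis names multiple imputation and intention-to-treat analysis of all enrolled participants. The most that can be said is that this wording sits in the fidelity paragraph and is not explicitly carried over to youth outcomes.

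**Fidelity.** The quintet is missing from that model too, but the size of the effect cannot be given. The ICCs under the fidelity power analysis are within-group, and nothing says how much of them lies between schools.

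**Conclusion.** The point holds in a conditional form. The mismatch between quintet randomisation and the stated models is plain from the text. Its effect depends on q, which is not given, and on whether the school level survives the ICC test.

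With the school level kept and 0.03 placed there, the overstatement for mobile versus standard runs from nothing at q = 0 to about 21% at q = 0.75. With the school level dropped, the standard error may be about 11% too small at q = 0. One specification that can err in either direction, depending on a significance test, is reason enough to change it.

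The baseline part is weaker: no error in inference, but a likely gain in precision that the plan does not clearly claim, sized only by an assumed correlation. The change is worth making because it costs so little; the planned sample size is not undermined.

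**What to change.** 1. Include quintet in every between-arm model (fidelity, other implementation outcomes, youth outcomes), either as nine fixed-effect terms or as a random effect.
2. Keep the school level whatever the ICC test shows, because the school is the unit randomised.
3. Name the baseline value as a covariate for each youth outcome and for EQ-5D.

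**Cost.** This changes analysis wording only and uses data the trial already plans to collect; the article reports that youth recruitment had not begun at submission. With fixed quintet effects, school-level degrees of freedom for mobile versus standard fall from 40 − 2 = 38 to 40 − 10 − 1 = 29. The two-sided 5% critical value rises from 2.02 to 2.05, and almost nothing is lost even if the matching turns out to explain no outcome variance.

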### Settings and participants

We will recruit 50 schools from the Western region of Sierra Leone to participate in the hybrid type 3 implementation-effectiveness cluster randomized trial. The Western region of Sierra Leone comprises two districts: Western Urban and Western Rural. The capital city of Freetown is located in the urban area of the Western region. English is the official language, and Krio is the lingua franca. According to the Sierra Leone Demographic and Health Survey in 2019 data on educational attainment in the Western Area, over 55% of men and 48% women have attained some secondary education. According to the 2020 Annual School Census report, there are 240 senior secondary schools in the Western Area (77 in Western Rural and 163 in Western Urban), which account for over a third (36%) of all senior secondary schools in the country. Most schools are co-educational, and just over half are public schools.

We will aim for balance in recruitment of schools from urban and rural areas. Potential schools in the Western region will be identified through publicly available databases maintained by the Government of Sierra Leone’s Ministry of Basic and Senior Secondary Education (MBSSE). Trained research assistants (RAs) (who have completed CITI training and training in good clinical practice) will use recruitment scripts to explain the study to eligible participants and determine if they are interested in participating. School eligibility criteria are: (a) a secondary school in the Western region that is (b) willing to provide the YRI as an extracurricular activity. RAs will first recruit and enroll principals (*N* = 50). RAs will obtain informed consent from interested principals of eligible secondary schools.

Principals who consent and enroll will then provide lists of teachers in their school. RAs will recruit four teachers per enrolled school (*N* = 160; 80 female/80 male). Teacher inclusion criteria are (a) currently employed as a teacher in a secondary school in the Western Region; and (b) willing to provide the YRI as an extracurricular activity. RAs will aim for gender balanced recruitment of teachers from enrolled schools because the YRI is delivered by gender-matched facilitators. RAs will contact teachers to describe the study and invite them to participate. RAs will obtain informed consent from interested teachers who meet eligibility criteria.

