#### Data collection

Data collection will be at three levels: teacher, principal and youth. Teachers (*N* = 160) and principals (*N* = 40) will complete quantitative assessments on implementation-level outcomes at baseline and post-intervention. All principals and a subset of teachers (*N* = 40) will also complete qualitative exit interviews at post-intervention to explore key aspects of feasibility, acceptability, and adoption, (e.g., usefulness of YRI skill-building exercises), and internal and external factors that might influence facilitator experiences (e.g., school climate, incentives). The subset of teachers will be selected based on a multivariate sampling matrix [31, 32]. We will also explore feasibility and acceptability of mobile-based supervision via key informant interviews with facilitators who received mobile supervision at post-intervention.

Youth (*N* = 1200) will complete quantitative assessments on mental health and daily functioning at baseline and post-intervention. Youth from intervention schools (*N* = 960) will complete quantitative assessments on implementation-level outcomes. A subset of youth (from intervention schools; *N* = 32) randomly selected based on a multivariate sampling matrix will complete exit interviews at post-intervention to obtain their feedback on YRI feasibility, acceptability, and barriers/facilitators to adoption. We will also collect data on educational outcomes for all youth via administrative records (i.e., school attendance, grades, tardiness, disciplinary reports) at baseline, post-intervention and 12-month follow-up. All youth will complete the EQ-5D-3 L at baseline, post-intervention and 12-month follow-up to inform the cost-effectiveness analysis [33].

Trained RAs will administer assessments electronically via tablets. All classroom instruction, assignments and tests are completed in English in our catchment area, thus the Western region schools, assessments and interviews will be completed in English as a first option. Versions of all study assessments will also be available in Krio (the local language) for any participants indicating difficulties with English fluency or a preference for completing assessments in Krio. All measures have been forward and backward translated from English to Krio previously. We will report data disaggregated by sex.

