### Trial status

At the time of manuscript submission, we had recruited and enrolled principal and teacher participants. Preparations were underway to begin youth participant recruitment.

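### Research assistants are declared blinded yet assign whole schools and do arm-dependent work, so their masking cannot hold as written; youth enrolment that appears to follow allocation risks selection between YRI and waitlist schools

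*Protocol article*

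**What the plan says.** The masking statement is one sentence under Study design: "All research assistants and data analysts will be blinded to participant assignment and will assign schools to study condition based on the allocation sequence". The same paragraph fixes the unit: "Randomization to study condition will occur at the level of the school". Schools are matched in fives before "randomly assigning two members of each quintet to each supervision model and the fifth to the control".

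The assistants' duties appear elsewhere. Under Settings and participants they "will use recruitment scripts to explain the study to eligible participants and determine if they are interested in participating", and they enrol principals and recruit teachers. The abstract's Methods ties the teachers to arm: "We will recruit and enroll four teachers per intervention-condition school". Under Data collection, "Trained RAs will administer assessments electronically via tablets". That section gives the implementation measures to 40 principals and to the 960 youth in intervention schools, out of 50 principals and 1,200 youth in all. The Measures section places these measures at baseline as well as post-intervention.

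On the order of events, Settings and participants says "We will recruit 480 youth from the 40 secondary schools randomized to receive the YRI delivered with mobile supervision", followed by the standard-supervision and control totals. Trial status reports principals and teachers as enrolled, and for youth says "Preparations were underway to begin youth participant recruitment". Youth eligibility includes ability and willingness to take part in an extracurricular activity. For control schools, Study design mentions only YRI training for interested teachers, after the 12-month follow-up.

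**The concern.** Two problems follow from these statements.

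The first is a contradiction. The group named as blinded is the group named as assigning schools. A reader who relies on the masking statement to judge the youth scales would be relying on something that the rest of the article rules out for the assistants.

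The second is a risk in enrolment. Randomizing schools balances schools. It does not protect against selecting individuals within a school once its arm is known. If the arm is known when youth are approached, agreeing to attend an activity means agreeing to a 12-session programme about to start in a YRI school, and to nothing imminent in a waitlist school. Different youth may agree. This would enter the YRI-versus-control effects and the QALY differences, for which the article says the control schools chiefly exist. An assistant's knowledge of arm when administering youth-reported scales is a second possible route to bias.

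**Working it through.** This is mostly a comparison of sections; the only arithmetic is a set of counts.

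1. **Counts behind the design.** Two mobile, two standard and one control school per quintet over 50 / 5 = 10 quintets gives 20 / 20 / 10 schools. At 24 youth per school: 20 × 24 = 480, 20 × 24 = 480, 10 × 24 = 240, total 1,200. The article's figures reproduce.

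2. **Assignment and blinding.** Arm is a property of the school. Assigning a school therefore means knowing the arm of all its participants. The two halves of the masking sentence cannot both be true of the same people, and the article names no separate allocator.

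3. **Teacher recruitment.** The stated total is 160. Four teachers in each of the 40 YRI schools gives 4 × 40 = 160; four in each of the 50 enrolled schools gives 4 × 50 = 200. Settings and participants words the rule as applying to every enrolled school but prints 160, so the number agrees with the abstract's rule. Assistants who recruit teachers only in intervention-condition schools can tell which ten schools are controls.

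4. **Assessment content.** Implementation measures go to 960 youth (480 + 480) and not to the 240 controls (1,200 − 960), and to 40 of 50 principals. An assistant who administers them can tell YRI schools from controls, already at baseline. App usability and the interviews with facilitators under mobile supervision identify the mobile arm to whoever collects them after the intervention.

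5. **Order of youth enrolment and allocation.** No sentence dates one against the other. Four features point to allocation first: youth are described as coming from schools randomized to an arm; teacher recruitment depends on arm; teachers were enrolled before youth recruitment began; and baseline implementation measures are arm-specific. The order is a well-supported inference, not a stated fact.

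6. **Which contrast is exposed.** Youth in both supervision arms are offered the same YRI, so willingness to attend means the same thing in both. The selection mechanism separates YRI from waitlist schools, not mobile from standard supervision.

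7. **Size.** The article gives no figure from which a difference in enrolment could be estimated. No sample-size figure changes.

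**The case against.** The strongest reply is that the masking sentence is a drafting slip that dropped an independent allocator, and that an article leaves to the full protocol who generates, holds and releases the sequence. The missing detail is indeed no finding. But the sentence makes a positive statement that is wrong as printed, and the teacher and assessment rules contradict assistant masking even if the sentence is repaired.

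Three stronger readings are tempting and do not stand:

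- **That masking fails altogether.** Analysts could still work on coded arms if they take no part in assignment. The supported statement concerns the assistants.
- **That youth are definitely recruited after randomization by unmasked staff.** The wording about randomized schools sits in forward-looking text, the schedule figure is not shown, and the sentence on youth recruitment does not name the assistants; only the general sentence about recruitment scripts does.
- **That the noninferiority comparison is biased by a calculable amount.** No enrolment mechanism is apparent between the two YRI arms. Setting an assumed shift against the 0.21 margin would only restate the assumption.

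Two further points reduce the concern without removing it. Youth are measured at baseline and student characteristics enter the level-one model, so imbalance in measured variables would be visible and partly adjustable; differences in unmeasured motivation would not. And the article says assessments are given on tablets without saying whether assistants read the items aloud, so the assessor route is possible rather than shown.

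**Conclusion.** The point holds in two parts of different strength. The contradiction is certain on the text: the declared masking of research assistants cannot hold as written, because they are named as assigning schools and because their recruitment and assessment tasks depend on arm. Differential enrolment of youth is a conditional risk. It rests on the inference that allocation is known when youth are approached, and it applies mainly to YRI-versus-control effects and QALYs. Its size cannot be estimated from the documents. Nothing here shows that the mobile-versus-standard comparison is biased or that analysts are unmasked. The masking text should be corrected, and the order of enrolment should be either protected or stated.

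**What to change.** - **Allocation.** Have the sequence applied and released by an existing staff member who does not recruit, assess or analyse. Keep analysts on coded arms. Reword the masking sentence to say who is blinded and to what.
- **Youth enrolment.** Complete youth enrolment and the baseline youth scales in all five schools of a quintet before its allocation is disclosed; with a two-two-one split, knowing four schools reveals the fifth. Arm-specific baseline implementation measures then follow release.
- **Where allocation is already known.** List eligible, willing students using one arm-neutral script, and draw the 24 (12 per sex) at random. This does not undo knowledge of the arm, but it removes discretion over who is picked from the list.
- **Post-intervention.** Administer the youth mental health scales and the EQ-5D-3L before any arm-specific implementation measure, where possible by an assistant who has not collected teacher or app data in that school. Coded arms alone would not mask assistants, because the implementation measures reveal YRI schools. If this ordering cannot be kept, withdraw the claim that assistants are blinded.

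The cost is a small scheduling effort: one task reassigned, enrolment and release reordered, and assistants rotated between schools. The article does not give the number of assistants, so how far rotation is feasible is for the trial team to confirm. Youth recruitment had not begun when the article was submitted, so the enrolment steps were still open then; the random draw is the fallback for schools whose arm was already known.
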